### Procedure

2.4

Individuals interested in participating will be guided via a secure hyperlink to the MobACT study platform (https://www.iterapi.se/sites/mobact/login) (Figure 2).

**Figure 2 F2:**
[figure not shown]
MobACT homepage. The homepage provides an overview of the project, including the research team, study aims, eligibility criteria, and a brief description of the MobACT intervention. It also includes access to the registration section for participant enrolment. Reproduced with permission from MobACT.

After providing informed consent, potential participants will complete an online screening assessment using standardized questionnaires (e.g., Web Screening questionnaire, WSQ) to determine preliminary eligibility. Moreover, within 5 days, they will attend a 30-min semi-structured clinical interview conducted by a licensed clinical psychologist not involved in the study, further assessing eligibility and clarifying study procedures. Eligibility decisions will be then jointly reviewed by the clinician and three principal researchers (Authors [name], [name] and [name]). Individuals will be informed of the decision via email within a week.

In cases of exclusion, a brief explanation of the decision will be provided. Individuals presenting severe psychological distress will be encouraged to seek appropriate professional support.

Randomization will occur after eligibility confirmation and completion of the baseline assessment. The allocation sequence will be computer-generated and implemented within the *Iterapi* platform, thereby ensuring allocation concealment until assignment. Due to the nature of the intervention, participants and clinicians involved in screening and intervention delivery cannot be blinded to group allocation.

Eligible participants will then be randomly allocated to either the intervention group, receiving the MobACT programme immediately or the control group (waitlist), receiving access to the programme after 7 weeks.

Participants will receive an email containing their username and a personalized link to create a password. Personal information will be anonymized by assigning each participant a unique identification code. Access to the intervention will be provided through a secure personalized login area on the *Iterapi* platform.

The *Iterapi* platform, developed at Linköping University, is a reliable system designed to deliver internet-based psychological interventions and to support research activities (Semonella et al., 2024a,b). The platform's architecture emphasizes security, process optimization and flexibility, and it supports multiple treatment modalities, including text-based communication, audio and video interactions (Vlaescu et al., 2016).

The platform is designed to be intuitive and user-friendly, ensuring seamless experience across devices such as desktop computers, tablets and smartphones.

*Iterapi* ensures data security and confidentiality through encrypted data transmission and secure storage. Study data is isolated, and access is restricted to authorized personnel only.

The *Iterapi* platform will be the main channel for communication between mental health professionals and participants, as well as for delivering the intervention and collecting quantitative assessments.

The treatment consists of seven modules (Figure 3), each addressing a specific component of psychological intervention based on ACT principles. The programme follows the procedures recommended by Hayes, Luoma (Hayes et al., 2006) and has been adapted from a Swedish ACT-based internet treatment that has already been tested and validated in previous clinical studies (Buhrman et al., 2013). Specifically, the content and functionalities of the program were tailored to the Italian general adult population and subsequently assessed for relevance, accessibility, and usability. The module topics are as follows:

**Introduction to the treatment:** This module introduces the concept of creative hopelessness. Participants are encouraged to reflect on their past attempts to control pain and to recognize the ineffectiveness of these efforts. This creates a foundation for acceptance and commitment to new strategies. The “Man in the Hole” metaphor is used to illustrate these ideas.**Willingness and Acceptance of Pain:** Participants learn to distinguish between primary and secondary pain. The concepts of willingness and acceptance are introduced. Metaphors such as the “Shark Trap” and the “Radio Metaphor” are used to illustrate the difference between short-term control and long-term acceptance (Figure 4).**Defusion from Negative Thoughts:** This module focuses on mindfulness and cognitive diffusion techniques aimed at helping participants distance themselves from negative thoughts and emotions. The “Bus Metaphor” is used, in which thoughts and emotions are conceptualized as passengers on a bus driven by the participant.**Committed Action and Values:** Participants explore their personal values and learn to cultivate a meaningful life despite the presence of pain. Exercises such as the “Chessboard Metaphor,” which distinguishes between the self and inner psychological content, as well as additional mindfulness practices, are used to facilitate value clarification.**Values and Goal Setting:** Building on the previous module, this section helps participants define and engage in actions aligned with their values. Exercises such as the “Values Compass” and metaphors including “The Skier” and “My Party” support this process.**Willingness Exercises:** This module provides a range of exercises designed to enhance participants' willingness to experience pain without attempting to control it. The “My Party” metaphor is used to demonstrate mindfulness in daily life and committed action.**Maintenance of Learned Strategies:** The final module includes the creation of a maintenance plan and a review of the goals established throughout the programme. It summarizes the entire intervention and offers guidance on how to sustain the strategies learned. Mindfulness practices are emphasized as a central component of the long-term maintenance plan.

**Figure 3 F3:**
[figure not shown]
Overview of the MobACT intervention modules. This figure illustrates the seven-module structure of the MobACT programme, outlining the sequence and thematic content of each weekly component of the intervention. Reproduced with permission from MobACT.

**Figure 4 F4:**
[figure not shown]
Module 2 – Chapter 10. Example of an ACT metaphor provided in the modules in both textual and audio form. This figure presents one of the ACT metaphors included in Module 2, Chapter 10 of the MobACT programme. The metaphor is available to participants in both written and audio formats, allowing them to engage with the material in the modality that best suits their preferences and learning style. This dual-format delivery aims to support accessibility and facilitate comprehension of key ACT concepts, particularly those related to willingness and acceptance. Reproduced with permission from MobACT.

Throughout the programme, participants will receive a weekly email every Thursday notifying them that a new module is available on the platform. Participants who do not access the material or complete the assigned exercises will receive a reminder email on Monday, including a brief standardized supportive message aimed at promoting clarification, encouragement, and engagement with the ACT-based activities.

At the end of the programme, participants in both groups will complete the post-intervention outcome assessments (T1), including measures of pain acceptance, pain intensity, pain interference, PF, psychological symptoms, sleep quality, coping strategies, self-efficacy, central sensitization, QoL, and anxiety and depressive symptoms. During the intervention period, participants will also complete brief weekly assessments within the platform, including a visual analog scale (VAS) evaluating perceived sleep quality and a brief item assessing changes in pharmacological treatment for chronic pain. If treatment changes are reported, participants will be asked to specify the nature of these modifications. The platform will allow real-time monitoring of missing or incomplete data, enabling the research team to send reminders or request clarification when necessary.

Following completion of T1 assessments, participants allocated to the waitlist control condition will receive access to the intervention, whereas participants in the experimental group will additionally complete follow-up assessments at 6 months post-treatment (T2).

No adverse or unintended effects related to trial participation are anticipated. However, participants experiencing psychological discomfort will be able to contact the research team for support. Any report of such difficulties will be reviewed by a trained clinician within the research team, who will evaluate whether follow-up is required. In the case of significant clinical concerns, particularly those related to suicidal ideation or risk, the established safety protocol will be applied, involving direct contact with the participant and referral to proper healthcare services. Participants may also contact the psychologist at any time in case of difficulties with the intervention material, questions regarding the exercises, or requests for further clarification. No scheduled therapist sessions will be provided during the programme. Participation is voluntary, and participants may withdraw from the study at any stage without consequences for their future care or treatment.

Throughout the trial, regular internal meetings will be held every 3 weeks to review recruitment progress, adherence levels, technical aspects of data acquisition and any issues arising during implementation. Deviations from the protocol, if any, will be documented, evaluated and reported according to ethical requirements and best practices for clinical research transparency. Upon completion of the trial, all monitoring activities and the integrity of the dataset will be reviewed before proceeding with final analysis.

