**Figure 1 F1:**
[figure not shown]
CONSORT flow diagram. As this manuscript describes a study protocol, participant flow is presented prospectively. Reasons for discontinuation, withdrawal or loss to follow-up will be collected at the time the event is identified. through a brief platform message, email or phone contact from a member of the research team. Reasons will be recorded using predefined categories (e.g., time constraints, technical difficulties, symptom worsening, perceived lack of usefulness, preference not to continue, adverse event, or other reason) and will be reported descriptively in the participant flow diagram whenever provided.

This study will be conducted in compliance with the Declaration of Helsinki and with all relevant national regulations governing research involving human participants. Ethical approval has been obtained from the Ethics Committee of Università Cattolica del Sacro Cuore, Milan (Approval Number: 146/24).

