**Depression**. The Patient Health Questionnaire (PHQ-9) (Kroenke and Spitzer, 2002) is a self-report instrument made up of 9-item used to assess depressive symptom severity. It screens eight psychological disorders, distinguishing between threshold DSM-IV diagnoses (major depressive disorder, panic disorder, other anxiety disorder, bulimia nervosa) and subthreshold conditions characterized by fewer symptoms than required for formal diagnosis (other depressive disorder, probable alcohol abuse/dependence, somatoform disorder, and binge eating disorder). Participants indicate how often each symptom has occurred over the past 2 weeks on a scale from 0 (“Not at all”) to 3 (“Nearly every day”), resulting in a total score from 0 to 27. Severity thresholds are 5 (mild), 10 (moderate), 15 (moderately severe), and 20 (severe depression), with scores ≥10 typically indicating clinically relevant depressive symptomatology. Item 9 assesses passive thoughts of death or self-harm and will be monitored according to trial safety procedures. The Italian version of the PHQ-9 has demonstrated good internal consistency (with Cronbach's alpha coefficients ranging from 0.86 to 0.92) (Mazzotti et al., 2003).

At each of the seven intervention weeks, participants will complete a VAS assessing their perceived sleep quality for that week (“How would you rate the quality of your sleep during this week?”), ranging from 0 (“worst imaginable sleep quality”) to 100 (“best imaginable sleep quality”).

Participants will also answer a weekly question regarding potential changes in their pharmacological treatment for chronic pain management.

**Week 1:** “Compared with what you reported at the pre-intervention assessment, have there been any changes in your pharmacological treatment for chronic pain management?”**Subsequent weeks:** “Compared with the previous week, have there been any changes in your pharmacological treatment for chronic pain management?”

Response options will be: “No, there have been no changes” or “Yes, there have been changes.” If changes are reported, participants will be prompted to specify the type of modification: “increased dosage of the same medication(s),” “reduced dosage of the same medication(s)” or “administration of different medication(s).”

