## Interim analysis and stopping guidelines

8

No interim analyses are planned for this trial, given the low-risk nature of the study. Therefore, no formal stopping guidelines have been established. Nevertheless, the study team will continue to monitor participants' safety throughout the trial, and the intervention delivery may be paused in the case of adverse psychological events.

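### Apart from PHQ-9 item 9, harms are recorded only passively, and the T1 scales collected in both arms are not assigned to a comparison of deterioration

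*Protocol article*

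**What the plan says.** Section 2.4 (Procedure) starts from the position that "No adverse or unintended effects related to trial participation are anticipated". It then says that "participants experiencing psychological discomfort will be able to contact the research team for support", and that a trained clinician reviews whatever is reported. A further route concerns the programme itself: "Participants may also contact the psychologist at any time in case of difficulties with the intervention material". Where there is serious concern, especially about suicide risk, a safety protocol of direct contact and referral applies.

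The note to Figure 1 (section 2.1) gives a second source: "Reasons for discontinuation, withdrawal or loss to follow-up will be collected at the time the event is identified". The predefined categories are "time constraints, technical difficulties, symptom worsening, perceived lack of usefulness, preference not to continue, adverse event, or other reason". They are reported descriptively, where the participant gives a reason.

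The description of the PHQ-9 in section 2.6.2 gives a third: "Item 9 assesses passive thoughts of death or self-harm and will be monitored according to trial safety procedures".

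Section 8 says that "the intervention delivery may be paused in the case of adverse psychological events" but not how such events come to light. Section 2.8 names no analysis of harms or deterioration. PHQ-9, GAD-7 and BPI are completed by both arms at T0 and T1 and are described as efficacy outcomes.

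**The concern.** Two of the three routes depend on the participant either writing in or leaving. The third is systematic but covers a single symptom. New or worse depression, anxiety or pain in someone who stays and keeps silent enters no harms record, although the trial will hold that person's T1 scores.

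The chance of being recorded may also depend on allocation. Before T1 the MobACT arm receives modules, Thursday notices, Monday reminders and a reason to contact the psychologist; the waitlist has no programme access. A small number of reports could then be taken as evidence of safety, and a difference in reports between arms could not be interpreted. Later analysis cannot recover events that nobody asked about.

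**Working it through.** The plan states no harms figure, so there is none to reproduce. The check sets the routes side by side and then shows the scale.

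**Routes before or at T1**

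| Route | Section | Who starts it | Both arms? | What it misses |
|---|---|---|---|---|
| General contact with the team | 2.4 | Participant | Not restricted by arm | Anyone who does not write |
| Psychologist contact about the material | 2.4 | Participant | In practice MobACT only before T1 | Waitlist; anyone who does not write |
| Reason for discontinuation, withdrawal or loss | 2.1, Figure 1 note | Team | Not restricted by arm | Anyone who stays; anyone who gives no reason |
| PHQ-9 item 9 | 2.6, 2.6.2 | Scheduled | Yes, T0 and T1 | Everything except thoughts of death or self-harm |

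The three-weekly meetings (sections 2.4 and 6) review recruitment, adherence, technical matters and implementation; they elicit no events from participants. Whether the waitlist completes the weekly sleep and medication items is not clear from the text.

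**Inputs.** Section 2.3 plans 140 participants, randomised 1:1, so 140/2 = 70 per arm. About 17% attrition leaves 140 × 0.83 = 116.2, or about 58 per arm at T1.

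**1. What zero reports would mean.** Volunteered reports need no T1 questionnaire, so the denominator is all 70 randomised to MobACT. The upper limit of the two-sided exact 95% interval for 0/70 is 1 − 0.025^(1/70) = 0.051. If only a fraction c of events is reported, the limit for the true rate is about 0.0513/c. The values of c are assumptions:

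| c | Upper limit |
|---|---|
| 100% | 5.1% |
| 75% | 6.8% |
| 50% | 10.3% |
| 25% | 20.5% |

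**2. What unequal reporting could do.** If the true rate is equal in both arms, the apparent risk ratio is the ratio of capture probabilities. Assumed capture of 80% in MobACT and 40% in the waitlist gives 0.80/0.40 = 2.0; the reverse gives 0.5. At an assumed true rate of 10%, 80% against 40% gives 70 × 0.10 × 0.80 = 5.6 recorded events against 70 × 0.10 × 0.40 = 2.8. The article fixes neither the size nor the direction.

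**3. What a T1 table could deliver.** With 58 per arm, the 95% half-width for a risk difference is 1.96 × √(2p(1 − p)/58). For assumed rates p of 5%, 10% and 20% this is 7.9, 10.9 and 14.6 percentage points. The table would describe harm; it would not exclude a moderate excess.

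**4. Whether that table would be free of bias.** Let true deterioration be 10% in both arms and missingness 17%, except among MobACT deteriorators, where it is m. The observed MobACT proportion is 0.10(1 − m) / [0.10(1 − m) + 0.90 × 0.83].
- m = 30%: 0.070/0.817 = 0.086, a risk ratio of 0.86.
- m = 50%: 0.050/0.797 = 0.063, a risk ratio of 0.63.

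The truth is 1.0 in both cases. The values of m are assumptions, but symptom worsening is a listed reason for leaving.

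**The case against.** The strongest reply is that this is a condensed article. It refers to a safety protocol and a supplementary checklist that are not shown, and harms tables commonly sit in the SAP. That stands for the table: its absence alone would not be a finding. It carries less weight for ascertainment, because the article does describe how harms reach the team, and the description is passive. The safety protocol, as described, governs the response once a concern is known.

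Four stronger readings are tempting, and the article does not support them:
- **A reader might infer that nothing is ascertained systematically.** Item 9 is scheduled in both arms and monitored.
- **A reader might infer that harms are captured unequally by arm.** General contact and withdrawal reasons are open to everyone. The extra programme contact makes a difference likely, but it remains an inference.
- **A reader might infer that volunteered reports will be compared between arms.** No such comparison is planned, and withdrawal reasons are descriptive.
- **A reader might infer that the trial cannot show whether MobACT makes people worse.** Average worsening would appear in the T1 secondary outcomes, and individual deterioration can be computed from the same scores. What is lacking is a commitment to do so.

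**Conclusion.** The point holds in a limited form. Apart from item 9, the harm routes described are passive, so a participant who deteriorates, stays and is silent is not recorded as a harm. Differential capture is likely but not demonstrated. Scales that would give a like-for-like view are already collected in both arms and are not assigned to that purpose.

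This is a weakness in a stated method that is cheap to improve; it is not a contradiction in the plan and does not affect the primary analysis. The 5.1% limit rests on 70 randomised to MobACT and complete reporting. The higher limits, the risk ratios of 2.0 and 0.5, and the attrition examples rest on assumed rates and show only what could happen. A T1 comparison should not be described as unbiased: outcomes are unblinded self-reports (section 4), and about 17% attrition is allowed for. Should the full protocol already contain scheduled adverse-event questioning in both arms, only the use of the T1 data would remain open.

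**What to change.** 1. Before outcome data are examined, pre-specify a T1 harms table by arm from data already collected. It should give the number with PHQ-9 item 9 ≥ 1 at T1, and the numbers worse than T0 on PHQ-9, GAD-7 and BPI by a threshold fixed in advance. An item 9 score ≥ 1 is an exclusion at screening (section 2.2), so a positive T1 response should usually be new; show the T0 response alongside, because the baseline assessment is described separately from screening.
2. Show the number with missing T1 data in each arm, with withdrawal reasons where given. Report risk differences with confidence intervals, and call the comparison symmetrically collected.
3. For participants not yet at T1, add one fixed question on unwanted effects or worsening, identical in both arms.
4. Report spontaneous contacts separately, without reading a low count as evidence of safety.

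Cost: the table needs no new data. The question needs a small amendment, since section 4 says that the trial has started, and it will be missing for anyone already past T1. Recorded harm counts will be higher than under spontaneous reporting, and the report should say why. No clinical procedure needs to change.

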### Qualitative component

2.5

Following completion of the intervention and the T1 assessment, approximately 20 participants from the intervention group will be invited to take part in a brief semi-structured interview exploring their subjective experience of the treatment programme and the digital platform (see Supplementary file 1). The qualitative component is included to complement quantitative findings by providing an in-depth understanding of participants' experiences, perceived usefulness of the intervention, barriers and facilitators to engagement, and overall treatment acceptability. Participants will be purposively sampled to maximize variation in relevant characteristics when possible, including age, sex, pain duration and level of intervention engagement. Interviews will be audio-recorded with consent and transcribed verbatim.

### Measures

2.6

During the initial screening phase, participants will complete the WSQ online (Pietrabissa et al., 2024). The WSQ consists of 15 items assessing a broad range of mental health problems, including depression, generalized anxiety disorder (GAD), panic disorder, agoraphobia, specific phobias, social phobia, post-traumatic stress disorder (PTSD), obsessive–compulsive disorder (OCD), alcohol misuse and suicidal ideation.

Developed at Vrije Universiteit Amsterdam, the WSQ is a brief internet-based tool designed to rapidly identify individuals at risk for common mental disorders. It requires approximately 2 min to complete and is used in this study to ensure adherence to inclusion and exclusion criteria. The WSQ effectively discriminates between individuals with and without psychiatric conditions; however, a positive screen requires further diagnostic evaluation (Pietrabissa et al., 2024). The Italian validation demonstrated good internal consistency (Cronbach's α = 0.732–0.891). Test–retest reliability showed high specificity for several disorders, including agoraphobia (0.947), anxiety (0.959) and panic disorder (0.973), as well as moderate sensitivity values.

At baseline, participants will provide self-reported demographic and clinical information, including age, gender, educational level, and marital status.

In addition, the Italian versions of the following psychological measures will be administered at baseline (T0), post-intervention (T1), and at the 6-month follow-up assessment (T2; intervention group only):

